### Secondary outcomes

#### Biopsychosocial questionnaires

Secondary biopsychosocial outcome measures of symptoms of depression, anxiety, and stress (Depression, Anxiety, and Stress Scale; DASS-12) [31], sleep impairment (Sleep Related Impairment—short; SRI-short) [32], pain (Brief Pain Inventory—short; BPI-short) [33], overall health (12-item Short Form Survey; SF-12) [34], complex post-traumatic stress disorder (Internal Trauma Questionnaire; ITQ) [35], alcohol and psychoactive substance use (Alcohol, Smoking, and Substance Involvement Screen Test—lite; ASSIST-lite) [36], and quality of life (World Health Organisation Quality of Life—abbreviated; WHOQOL-BREF) [37]. All secondary outcome measures are included in Table 1.

**Table 1 Tab1:** Primary and secondary outcome measures

Outcome	Outcome measure
Primary	
PTSD symptom burden	The Posttraumatic Stress Disorder Checklist (PCL-5)
Secondary	
Exercise tolerance	Buffalo Concussion Bike Test (BCBT)—Max HR achieved, HRV metrics
Depression, anxiety, and stress	Depression, Anxiety & Stress Symptom Scale (DASS-12)
Complex post-traumatic stress disorder	International Trauma Questionnaire (ITQ)
Substance use	ASSIST-LITE
Pain	Brief Pain Inventory
General health	12-Item Short Form Health Survey (SF-12)
Sleep	Sleep-related inventory—short (SRI-short)
Concussion-like symptom burden	Rivermead Post‑concussion Symptoms Questionnaire (RPQ)
Quality of life	World Health Organisation Quality of Life (WHOQOL-BREF)
Cognitive outcomes	Cognitive performance at baseline compared to follow-up Rey Auditory Verbal Learning Test WAIS-IV Working Memory Index—subtests Digit Span, Letter Number Sequencing Oral Symbol Digit Modalities Task Trail Making Test
Blood biomarkers	Inflammatory factors (e.g. IL-1β, IL-18) Growth factors (e.g. VEGF, BDNF)
Compliance and feasibility	Weekly follow-up survey and verified via Fitbit reports
Safety and tolerability	Adverse events reported throughout 4 weeks during daily exercise

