### Objectives

The primary objective is to determine the effects of a 4-week program of structured aerobic exercise on PTSD symptom burden in women IPV victim-survivors compared to those who complete a program of 4 weeks of passive stretching. The secondary objective is to determine the effects of the exercise intervention on biopsychosocial measures (i.e. quality of life, depression, anxiety and stress, concussion-like symptoms, sleep), cognitive performance, and blood biomarkers related to inflammation and growth factors compared to passive stretching.

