#### Cognitive measures

Cognitive outcome measures include the Test of Premorbid Functioning (TOPF) [38], Rey Auditory Verbal Learning Test (RAVLT) [39], Digit Span (DS) [40], Oral Symbol Digit Modalities Test (O-SDMT) [41], and the Trail Making Test parts A and B (TMT) [42].

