### Assessment and collection of outcomes

Participants will be assessed at baseline (day 0) and at the primary endpoint (day 28). During the trial, participants will return and be re-evaluated weekly on PTSD symptoms, BCBT, biopsychosocial questionnaires, and fluid biomarkers. In addition to exercise compliance, medications, and therapies, as well as any adverse events, compliance and feasibility will be evaluated at the weekly follow-up appointment. Cognitive assessment will only be repeated on the final evaluation. All data collection will occur at the Alfred Centre, Monash University. The full study schedule is included (Table 2).

**Table 2 Tab2:** Study schedule

Study assessments	Screening	Baseline	Intervention period	Weekly follow-up	Final visit
		Day 0	Day 1–6; day 8–13; day 15–20; day 22–27	Day 7, 14, 21	Day 28
Screening					
Eligibility questionnaire	X				
Enrolment					
Inclusion/exclusion criteria review	X	X			
Informed consent		X			
Allocate unique subject study identification		X			
Questionnaires					
Demographic data		X			
Medical history		X			
Ohio State University TBI Identification Method		X			
Godin Leisure-Time Exercise questionnaire		X		X	X
Medications		X		X	X
Current therapies		X		X	X
Exercise tolerance test					
Buffalo Concussion Bike Test (BCBT)		X		X	X
ECG recording		X		X	X
Biopsychosocial					
PTSD symptomology: PCL-5	X	X		X	X
Rivermead Post-Concussion Symptoms Questionnaire (RPQ)		X		X	X
Depression, Anxiety & Stress Symptom Scale (DASS-12)		X		X	X
The Alcohol, Smoking and Substance Involvement Screening Test (ASSIST-LITE)		X			X
Brief Pain Inventory (BPI)		X			X
12-Item Short Form Health Survey (SF-12)		X			X
World Health Organisation Quality of Life (WHOQOL-BREF)		X			X
Sleep-related inventory (SRI)		X			X
International Trauma Questionnaire (ITQ)		X			X
Neuropsychological assessment					
TOPF		X			
RAVLT		X			X
Digit Span		X			X
O-SDMT		X			X
TMT		X			X
Biomarkers					
Blood sample collection		X		X	X
Therapeutic intervention					
Dispense intervention		X		X	
Fitbit—dispense and instructions		X			
Record daily intervention sessions			X		
Return of Fitbit					X
Safety and feasibility assessments					
Adverse event monitoring		X		X	X
Feasibility					X

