### Data analysis

Primary and secondary outcomes will be assessed between groups at the primary endpoint (week 4) using two-sample *t*-tests (if normally distributed) or Mann-Whitney *U* tests (if not normally distributed). In addition, variables with multiple time points will also be assessed using generalised linear mixed-effects models. Models will be adjusted for confounders such as age, sex, baseline depression/anxiety/stress, history of migraine or other comorbidities, and cardiovascular fitness (Godin assessment). Feasibility (recruitment, retention, and completion rates), adherence (proportion), and safety (number and types of adverse events) will also be assessed. A statistician will be consulted in the events of missing data, any additional analysis, and to advise on interim analyses and stopping guidelines. Participants who do not complete the full 4-week intervention (i.e. lost to follow-ups) will be excluded from the primary endpoint analysis however will be retained in the descriptive analyses of the feasibility outcomes. Only the principal investigator will have the authority to terminate the trial.

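### The week-4 test of the cognitive outcomes ignores each test's own baseline score, and Table 1 does not say whether the variable is the day-28 score or the change

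*Protocol article*

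**What the plan says.** All of the following is in the protocol article.

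- **Objectives.** The secondary objective covers "cognitive performance, and blood biomarkers related to inflammation and growth factors compared to passive stretching". This is a between-arm question.
- **Table 1 (Secondary outcomes).** The cognitive row reads "Cognitive performance at baseline compared to follow-up" and then lists "Rey Auditory Verbal Learning Test WAIS-IV Working Memory Index—subtests Digit Span, Letter Number Sequencing Oral Symbol Digit Modalities Task Trail Making Test". The text before the table says "All secondary outcome measures are included in Table 1". The TOPF is not in the table.
- **Cognitive measures.** The text begins "Cognitive outcome measures include the Test of Premorbid Functioning (TOPF", followed by the RAVLT, Digit Span, O-SDMT and TMT.
- **Assessment and collection of outcomes.** "Cognitive assessment will only be repeated on the final evaluation". Table 2 marks the RAVLT, Digit Span, O-SDMT and TMT at day 0 and day 28, and the TOPF at day 0 only.
- **Data analysis.** "Primary and secondary outcomes will be assessed between groups at the primary endpoint (week 4", by two-sample t-test or, if the data are not normal, by Mann-Whitney test. The next sentence adds that "variables with multiple time points will also be assessed using generalised linear mixed-effects models". The models are adjusted for confounders, with age, sex, baseline depression/anxiety/stress, migraine or other comorbidities, and the Godin score given as examples.

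**The concern.** Each repeated cognitive test is taken once before randomisation and once at day 28. The first-named analysis uses only the second score. Stable differences in ability between women then stay in the error term, although the trial has measured them with the same test.

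Table 1 does not settle which variable is analysed. Its wording fits a day-28 score read against baseline, and it also fits a change from baseline. Unlike most other rows of that table, it describes a comparison, but the comparison is over time, and the arm contrast required by the Objectives is left unsaid.

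An analyst could therefore use a raw day-28 test, a change score or a mixed model, and the text does not say which result counts. These have different precision, so the trial's ability to detect an effect on cognition depends on a choice that the article leaves open.

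**Working it through.** **Inputs**

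- Completers: the Sample size section gives 120 recruited and 20% drop-out, so 120 × 0.80 = 96, or 48 per arm if the arms are equal. Simple 1:1 randomisation makes equal arms the expectation, not a guarantee.
- Two-sided 5% level and 80% power: assumed, because the article states neither. The normal quantiles are 1.96 and 0.842.
- Correlation r between baseline and day-28 scores on the same test: not in the article. Assumed to be 0.6, 0.7 or 0.8.

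The article gives no detectable difference for cognition, so there is no figure of its own to reproduce.

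**Unadjusted day-28 test**

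Detectable difference = (1.96 + 0.842) × √(2/48) = 2.802 × 0.2041 = 0.572 SD.

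**With baseline.** Multiply by √(2(1 − r)) for a change score, or by √(1 − r²) for the day-28 score with baseline as covariate.

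| r | Unadjusted day 28 | Change score | Day 28, baseline as covariate |
|---|---|---|---|
| 0.6 | 0.572 | 0.572 × 0.894 = 0.511 | 0.572 × 0.800 = 0.457 |
| 0.7 | 0.572 | 0.572 × 0.775 = 0.443 | 0.572 × 0.714 = 0.408 |
| 0.8 | 0.572 | 0.572 × 0.632 = 0.362 | 0.572 × 0.600 = 0.343 |

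At r = 0.7, an unadjusted test would need 48 / (1 − 0.49) = 94 women per arm to match the precision of the covariate-adjusted comparison with 48.

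**What the mixed models add.** The repeated cognitive tests have two time points, so the mixed-model sentence covers them, and such a model can use the baseline score. The text does not say how. If baseline is a response and the arms may differ there, the arm-by-time term with complete data is the difference in change (third column). If the arm means are constrained to be equal at baseline, the result is close to the last column. The sentence makes these models additional to the week-4 test and gives neither analysis precedence.

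**TOPF.** Cognitive measures calls it an outcome measure. Table 1, described as complete, omits it, and Table 2 schedules it at day 0 only. Two of the three places treat it as something other than an outcome, so the label in Cognitive measures is the odd one out.

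**The case against.** The case against has five parts.

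- **The plan does not rest on week-4 scores alone.** This stands. A reader who stops at the first sentence of Data analysis might infer that baseline scores are never used, but the mixed models can use them. What remains is that they are secondary in wording and do not name the test's own baseline score. The list of adjusters is introduced as examples, so that score is not excluded either.
- **Table 1 does not contradict the analysis section.** This also stands. The row can be read as change compared between arms, which fits both the Objectives and the between-group wording. It is an ambiguity. A reader might infer a planned before-after test within one arm, in which gains from retesting would pass for a treatment effect. No section plans such a test.
- **The precision gain is generic.** It is: it would apply to any continuous outcome measured at baseline and tested this way. That does not make it less available here.
- **Covariates belong in an analysis plan that is not shown.** This would answer silence. The article is not silent: it fixes a named, unadjusted test for week 4.
- **The TOPF is only mislabelled.** Agreed. A reader might infer that an impossible week-4 TOPF comparison has been promised. Data analysis never names the TOPF, and Table 1 leaves it out of the secondary outcomes. The sentence about repeating the cognitive assessment restricts its timing and does not say that every test is repeated.

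**Conclusion.** The point holds as an avoidable loss of precision together with an imprecise outcome definition. As stated, the week-4 comparison of the cognitive tests discards a baseline score that is already collected, and Table 1 does not fix the variable or the contrast.

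Under the assumed correlations of 0.6 to 0.8, using that score lowers the detectable difference from about 0.57 SD to between 0.46 and 0.34 SD, and to about 0.41 SD at 0.7. These figures assume 96 completers split equally, 80% power at the two-sided 5% level, and equal SDs at both visits and in both arms. The gain shrinks if the true correlations are lower. It should be set against the raw week-4 test only, since the additional mixed models may recover much of it, depending on how they are specified.

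The matter is confined to secondary outcomes and does not touch the primary analysis or the sample size. The TOPF item is a minor consistency correction.

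**What to change.** 1. **Data analysis.** State that each repeated cognitive test is analysed as the day-28 score, compared between arms with that test's own baseline score as covariate, and that this is the main analysis for cognition. Keep any approach for non-normal scores baseline-adjusted as well. If the mixed model is retained, say how baseline enters and that it is supportive.
2. **Table 1.** Reword the cognitive row to the day-28 score on each repeated test, aerobic exercise versus stretching, adjusted for baseline.
3. **Cognitive measures.** Relabel the TOPF as a baseline descriptor. Using it as a further covariate is optional.
4. **Consistency in the same edit.** Letter Number Sequencing is in Table 1 but in neither Cognitive measures nor Table 2. The Abstract includes cognitive testing among outcomes collected weekly, whereas Assessment and collection of outcomes limits the repeat to the final visit. Reconcile both.

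The cost is wording only. For the four tests that Table 2 schedules twice, the baseline and day-28 scores are already being collected. Recruitment was still under way at submission, so the change can be made before the data are analysed.

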#### Cognitive measures

Cognitive outcome measures include the Test of Premorbid Functioning (TOPF) [38], Rey Auditory Verbal Learning Test (RAVLT) [39], Digit Span (DS) [40], Oral Symbol Digit Modalities Test (O-SDMT) [41], and the Trail Making Test parts A and B (TMT) [42].

#### Concussion-like symptoms

Mild traumatic brain injuries (mTBI) are reported in up to 92% of women IPV survivors [43], with non-fatal strangulation events and subclinical head traumas also commonly described and potentially contributing to brain pathology. Aerobic exercise has proven to promote recovery in adolescents with persisting concussion symptoms due to sports-related concussions [26, 44–46], and modulate concentrations of brain-specific and systemic blood biomarkers associated with inflammation and vascular and neuronal growth [47–50], many of which have been shown to be dysregulated in individuals with PTSD [51–53] and in rat models of IPV-related brain injury [54]. Therefore, here we will also be documenting each participant’s history of brain injury and measuring the impact of the intervention on concussion symptoms (Rivermead Post-Concussion Symptom Questionnaire; RPQ) [55].

#### Blood-based biomarkers

Approximately 30 ml of venous blood will be collected from each participant at baseline and all follow-up assessments by a trained staff member or physician. All blood samples will be centrifuged to collect serum and plasma, coded with the participant’s unique “Study ID”, and stored in a −80-degree freezer until analysis. Access to biomarker data will be restricted to only the investigators of the study. Biomarkers of interest include those associated with inflammation (e.g. IL-1β, IL-18) and growth factors (e.g. BDNF, VEGF).

#### Exercise tolerance and the Buffalo Concussion Bike Test

Exercise intolerance (i.e. the inability to exercise at or near to age-appropriate maximum HR due to exacerbation of concussion-like symptoms) has been reported in adults with mTBIs and/or PPCS [56] but has not been directly studied in women victim-survivors. Exercise tolerance will be measured using the BCBT and is used to determine the HR at which concussion-like symptom exacerbation occurs (i.e. HR threshold [57, 58]). If a participant is experiencing no symptoms or no exacerbation occurs during the BCBT, the patient is determined to be exercise tolerant. During the BCBT, participants are asked to cycle on a stationary seated bike at a determined revolutions per minute (RPM). Every 2 min, bike resistance will increase, and participants will indicate their rate of perceived exertion using the Borg Ratings of Perceived Exertion (RPE) [59] 6–20 (lowest to highest), and concussion-like symptom onset using the VAS [60]. The height and weight of each individual participant determine bike resistance levels and RPM. HR will be recorded with the Fitbit (Inspire 3) and an electrocardiogram (ECG) (PowerLab 16/36 with Dual Bio Amp; LabChart 8). According to Haider et al. [57] and Leddy and Willer [58], the BCBT is terminated when (1) the participant self-reports reaching an 18 on the RPE, (2) HR on the ECG reaches 80% of age estimated HR-max ((220 − age) * 0.8), (3) the participant self-reports a 3-point increase on the VAS, or (4) the exercise test reaches 30 min. Once the test is finished, bike resistance is brought to zero, and the participant will continue to cycle at their own pace for a 2-min cool down. Following the BCBT, participants will be randomised to either the exercise or the stretching intervention using simple randomisation.

## Data collection, management, and analysis

### Trial allocation

This study is an open-label study; therefore, the investigator, site staff, and subjects will not be blinded to treatment allocation. A computer-generated randomisation schedule will be prepared by a statistician prior to the start of the study. Treatment allocation will be made per the randomisation list. After signing the informed consent form, subjects will be allocated a unique subject ID and administered the screening instruments via Research Electronic Data Capture (REDCap). A unique subject ID will be used to identify the subject throughout the study period and on all study-related documentation. After eligibility has been established, subjects will complete all baseline assessments followed by a simple randomisation in a 1:1 ratio to either the aerobic exercise or stretching group. Randomisation will be allocated sequentially based on the pre-determined randomisation schedule and according to their chronological order of inclusion in the study.

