### Study outline

The trial will encompass a total of 5 sessions over 4 weeks. Participants with low exercise risk will meet a researcher in person at the Alfred Centre for baseline and subsequent weekly follow-up assessments thereafter. Daily exercise or stretching will be performed by the participants at their own discretion. A flowchart of the study timeline is provided in Fig. 1.

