### Data management and storage

All data will also be coded in a re-identifiable manner and securely stored via REDCap on the Monash University server. A master code linking re-identifiable details will be kept in a secure password-protected database REDCap. The manager of the linking data is PI [name]. Only researchers who are actively contributing to data collection, statistical analysis, and publication will have access to the data. Any hardcopy data will be stored in a locked drawer in the Alfred Centre, accessible only by the investigators. All fluid-based samples will be coded (i.e. re-identifiable) and stored in an ultralow temperature (−80 °C) freezer housed in labs within the Department of Neuroscience, Monash University, until they are analysed. The freezer will only be accessed by the investigators of this study. During the study, participants will be required to wear a Fitbit (Inspire 3) activity tracker. The device must be paired to their mobile phone and synced to the research platform Fitabase. Only data related to HR, steps taken, activity intensity, calories burned, and sleep rating will be collected. No other data from their mobile phone or daily life will be exported to the institute. It is important to note that the collected data will be used solely for the purposes of the study and will be kept confidential. Given that this study involves self-directed aerobic exercise among participants screened via the PAR-Q and assessed for cardiovascular risk, a data safety monitoring board was not considered necessary. Further, as this trial will be conducted at a single site, oversight of the trial will be managed by the research team. As such, a steering committee and data quality committee were not deemed necessary.

Any amendments to the study protocol will be sent to the Monash Human Research Ethics Committee and will not be implemented until approval. Amendments will also be sent to the PI to be added to the Investigator Site File. Any deviations from the approved protocol will be documented using a breach report form.

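### Open-label status is applied to the investigator and site staff as a whole, and no masking is set out for the biomarker assays or the data-dependent analysis choices, although neither needs knowledge of the arm

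*Protocol article*

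**What the plan says.** All references are to the protocol article.

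- **Trial allocation:** "This study is an open-label study; therefore, the investigator, site staff, and subjects will not be blinded to treatment allocation". The section makes no exception for any task.
- **Blood-based biomarkers:** "Access to biomarker data will be restricted to only the investigators of the study". Samples carry the participant's Study ID and stay frozen until analysis.
- **Data management and storage:** "The freezer will only be accessed by the investigators of this study", and "All fluid-based samples will be coded (i.e. re-identifiable"). On the data in general: "Only researchers who are actively contributing to data collection, statistical analysis, and publication will have access to the data". The principal investigator manages the linking data.
- **Data analysis:** the choice between a t-test and a Mann-Whitney test depends on whether the data look normal. The covariate list is given as examples and includes unspecified comorbidities. Missing data and additional analyses are settled in consultation with a statistician when they arise.

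No section provides for the arm to be hidden at assay or at analysis. No section says who runs the assays or who carries out the analysis.

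**The concern.** The word linking the two halves of the Trial allocation sentence carries an inference that does not hold. Exercise and stretching cannot be disguised from the women doing them, or from staff who prescribe a target heart rate and check it. That says nothing about a person running a cytokine plate or deciding whether a variable is normal enough for a t-test.

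Two things are at stake.

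- **Biomarkers.** These are meant to give mechanistic insight and possibly objective markers, and they are among the outcomes least dependent on self-report. That value is reduced if re-runs and outlier exclusions are decided with the arm in view.
- **Analysis.** Several choices are made after the data are seen. Someone who knows the arm can be influenced, without intending it, by which choice favours which group. This applies to the primary outcome as well.

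**Working it through.** **1. What the rule covers, task by task**

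| Task | Does the task require the arm? | What the article provides |
|---|---|---|
| Doing the exercise or stretching | Yes | Unblinded |
| Prescribing and monitoring heart rate or stretching | Yes | Unblinded (site staff) |
| Running assays, re-runs, outlier exclusions | No | Samples and biomarker data open to the investigators only; coded by Study ID but re-identifiable; nothing says the arm is hidden |
| Choosing test, covariates and additional analyses | No | Choices left open; no masking set out |

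The first two rows justify open-label status. The last two do not follow from it.

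**2. Does Study ID coding already mask the assays?** Only in part. Trial allocation uses one subject ID throughout the study and on all study documents. The samples are described as re-identifiable, and the master code is held within the team. An unblinded member of that team who sees an ID may be able to recall or look up the arm. Equally, nothing says that the arm is visible at the bench.

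**3. The plan's own figure.** Sample size gives earlier trials of 46 to 96 participants, 20% drop-out and a target of 120. Starting from 96: 96 / (1 − 0.20) = 120, which reproduces the target. Completers expected: 120 × 0.80 = 96, or 48 per arm on average under 1:1 allocation. The fix does not change this number.

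**4. Illustration of what a bias could do.** The documents give no size for observer bias, so the shift b (in SD units) is an assumption. With no true effect, n = 48 per arm, a two-sided 5% level and a normal approximation:

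- Noncentrality = b × √(n/2) = b × √24 = b × 4.899
- False-positive rate = Φ(nc − 1.96) + Φ(−nc − 1.96)

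| Assumed shift b | Noncentrality | False-positive rate |
|---|---|---|
| 0 | 0 | 5.0% |
| 0.1 SD | 0.49 | 7.8% |
| 0.2 SD | 0.98 | 16.5% |

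These rates apply to a single outcome affected by such a shift. They show sensitivity at this sample size and are not an estimate for this trial.

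**The case against.** **The article does not say that unblinded people do this work.** This is correct. A reader might infer that the unblinded investigators run the assays, score the cognitive tests and analyse the data. The access rules make that plausible, but no section states it. Trial allocation names neither laboratory staff nor the statistician. The point therefore rests on the breadth of the stated rule and the absence of any exception to it.

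**Masking of assays and analyst may be in the full protocol or an analysis plan.** It may. Silence in a condensed article would be no finding. Here, however, the article states a rule and gives a reason that does not support its scope. If masking is set out elsewhere, the sentence still needs correcting to agree with it.

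**Samples are already coded.** This stands as partial protection, within the limits shown in the working.

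**The primary outcome is barely touched.** This is largely right. A reader might infer that masking would protect the trial's main result. The PCL-5 is rated by women who know their arm, and no masking of assays or analyst removes that. Masked analysis choices limit only selective analysis of it.

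**Cognitive testing is exposed too, so mask the examiners.** A researcher sees participants in person, and "Cognitive assessment will only be repeated on the final evaluation", after allocation is known. But Table 2 places the bike test, adverse-event review and feasibility assessment at the same day-28 visit, so a masked examiner may need extra staff. With recruitment under way, a new rule could also mix masked and unmasked assessments. A reader might infer that this could be had at no cost; the documents do not support that.

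**A/B coding can be broken by the data.** This is a fair practical point. Adherence is calculated against a target heart rate, and such fields could reveal the arm. The fix has to withhold them.

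**Conclusion.** The point holds in a limited form. The article derives unblinding of the investigator and site staff as a group from open-label status. It restricts samples and biomarker data to the investigators, and it sets out no masking for two activities that do not need the arm. It is worth correcting because the remedy is cheap and because knowledge of the arm cannot be undone once assays and analysis decisions have been made with it.

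The benefit falls mainly on secondary biomarker outcomes and on protection against selective analysis. Its size is unknown: 7.8% and 16.5% depend entirely on assumed shifts of 0.1 and 0.2 SD with 48 completers per arm. The conclusion also assumes that no other trial document already hides the arm at assay and analysis.

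**What to change.** 1. Limit the unblinding sentence in Trial allocation to participants and the staff who deliver or monitor the intervention.
2. State that assays, re-runs and outlier exclusions are done on Study ID with the arm hidden from whoever makes those decisions.
3. State that the analyst receives the arm only as A/B until biomarker exclusions, choice of test, covariates and code are fixed and recorded. Withhold adherence, target heart rate and any other field that shows the arm until then.
4. Say who runs the assays and who performs the analysis. If the statistician who prepared the randomisation schedule is also to analyse the data, someone else should assign the A/B labels.

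The cost is a restricted REDCap field, a few sentences in the protocol and a short delay in unmasking for analysis. No visit, treatment or sample size changes. Recruitment was still open at submission, data collection is expected to end on 16/05/2027, and samples are stored frozen, so the change can apply to all assays and analyses not yet done. If some have been done already, report which.
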